### Sustainability

We expect a limited amount of decline in physiologic outcomes with the transition back to usual care. We will test the hypothesis that improvements in A1c, blood pressure, and LDL cholesterol will be maintained during the maintenance time period. The analyses will be conducted similarly as for H1, and will evaluate change in the initial intervention group one year after intervention completion.

Consulting with [name], we will implement a *Sustainability Action Plan (SAP)* to integrate HCs and ensure provision of pharmacy telehealth at an organizational level beyond the period of grant funding. The first phase will identify existing organizational goals and activities that support integration of HCs and pharmacy telehealth approaches into routine clinical operations. Our healthcare system is actively testing HC/peer educator models in multiple locations of the network. In collaboration with these sites and other key stakeholders, we will adapt an existing sustainability checklist to evaluate the presence of specific factors that are needed to support on-going operations within the organization. The next phase involves identifying existing and needed resources within our organization to support delivery of the additional services at the end of the study. The cost-effectiveness data (Aim 3) will help guide this procedure. Working with the Illinois Healthcare Reform Implementation Council and our existing relationship with the Illinois Community Health Worker Advisory Board (see letter of support), we will share details on training and reimbursement for community health workers (aka health coaches) as set forth in the Affordable Care Act and Illinois Bill HB5412 (the board will propose training and certification processes for community health workers and advice legislators). [name] (consultant), as the Global Director of Peers for Progress, is actively involved in legislation to provide peer support service reimbursement and will aid in identifying relevant stakeholders. The final step focuses on executing the outlined action plan.

**Table 4: RE-AIM Framework for Process Evaluation**

|                       |                                                                                                                                                                                                                                                                                    |
|-----------------------|------------------------------------------------------------------------------------------------------------------------------------------------------------------------------------------------------------------------------------------------------------------------------------|
| Reach          | Identify proportion of eligible population contacted, responded, participated, and excluded. Compare demographics and glycemic levels of eligible UI Health patients and study participants. Are the study participants representative of the clinical population?                 |
| Effectiveness  | Determine change in hemoglobin A1c, blood pressure, and other outcomes (Aim 1). Are there unintended consequences of the intervention (e.g., negative impact on quality of life)?                                                                                                  |
| Adoption       | Conduct semi-structured interviews with randomly selected providers, staff, administrators, and health coaches across participating clinical sites (interview guides to be developed). Assess satisfaction and compare resources, setting, and intervention delivery across sites. |
| Implementation | Measure HC activity including encounters and phone calls completed, videoconferencing, and text messages delivered. Determine subject participation in intervention.                                                                                                               |
| Maintenance    | Implement Sustainability Action Plan (Aim 2). Evaluate change in outcomes one year after completion of the intervention and determine if positive outcomes were maintained. Assess drop-out rates and adverse events experienced.                                                  |

Process evaluation will provide support for the project's potential as an intervention in a real-world setting. We will evaluate translation using the RE-AIM framework to determine dissemination potential and generalizability (Table 4). To assess adoption, we will conduct semi-structured interviews of providers, staff, and administrators, providing different perspectives.

Chain sampling will help identify those most likely to be “information rich” and continue until saturation reached.

Pharmacist interviews: Up to 15 pharmacists who have participated in the mHealth for Diabetes Adherence Support study (IRB 2016-0380) will be individually interviewed to gather feedback on delivering the intervention and potential for adoption.

An email invitation will be sent to pharmacists describing the purpose of the interview and a summary of the procedures. Interested pharmacists will be scheduled for one-on-one interviews with [name] or a research assistant. The interviews will take place in private room at the pharmacist’s clinical site or at a private campus location that is convenient for the pharmacist. A semi-structured interview guide will be used and content will focus on video conferencing, provider-pharmacist interactions, and interactions with health coaches. Interviews will be audio recorded. Names of the pharmacists will not be linked to their responses in order to maintain confidentiality. A brief demographic survey will be completed by the pharmacist and a number will be assigned to their interview. The interview will last approximately 30 minutes.

Interviews will be transcribed, coded and analyzed. Results will be used to inform the process evaluation component for the study (Aim 4) and future research involving clinical pharmacists, health coaches and the use of telehealth technology in health care.

### Cost and Cost Effectiveness

We will obtain program and healthcare use data to estimate the cumulative costs from a health system perspective for each group over 24 months. To accommodate drop-outs and missing data (censoring) in the cost estimates, we will use a modification of survival analysis. To estimate average cumulative costs, we will divide the time interval following randomization into months, and then estimate cumulative costs to time  $T$  (i.e., 6, 12, 18, and 24 months) as:  $C_{(T)} = p_t \times c_t$ , where  $p_t$  is the probability of participating at month  $t$ , and  $c_t$  is the mean cost at month  $t$  given participation at  $t$ . Patients participating at the end of follow-up contribute cost information from randomization to end of follow-up, while patients who drop out contribute costs from randomization through drop-out date (and then zero costs thereafter until end of subject follow-up). We will then discount to estimate the average present value of costs:  $C_{(T)} = \sum_{t=1}^T \hat{S}_t \bar{C}(t) / (1 + r)^{t-1}$ , where  $r$  is the discount rate and  $\hat{S}_t$  is the Kaplan-Meier estimator of the probability of participation to month  $t$ . We will use a discount rate of 3% per year and calculate  $C_{(T)}$  for subjects in both groups. For the cost-effectiveness analysis, we will calculate the incremental average costs resulting from *mDAS* vs. usual care and compare via a two-sample  $t$ -test for independent groups. Costs may not be normally distributed; however, if the sample is sufficiently large,  $t$ -tests on untransformed costs are appropriate.

Our effectiveness measures will include improvements in A1c, blood pressure, of cholesterol levels and projected quality-adjusted life-years (QALYs). Furthermore, a reduction in unnecessary healthcare utilization (emergency room visits and preventable hospitalizations) may result in cost savings. The incremental cost-effectiveness ratio (e.g., cost per change in A1c) of *mDAS* vs. usual care will be estimated at the end of 12 and 24 months. Cost per QALY will be determined from projections of continued mHealth involvement and assumptions concerning

the continued effects of *mDAS* on outcomes over time. The QALY and utility estimates will be based on the Markov model developed by the Diabetes Cost-effectiveness Group at the CDC (using UKPDS data). Sensitivity analyses will estimate the impact of changes in factors such as age, induced health-care visits, incidence of complications, HC costs, physician time, and discount rates. We will discount both QALYs and costs at 3% per year to maintain equivalent treatment of the measures of costs and effectiveness over time. To compare discounted QALYs, we will integrate the area under the Kaplan-Meier curves for each study condition to obtain mean QALYs. The difference between the two areas will provide the incremental effectiveness from receiving *mDAS*.

The ratio of net costs ( $\Delta$  costs) and net utility ( $\Delta$  utility) will yield the incremental cost utility ratio between the *mDAS* and usual care groups. One-way sensitivity analyses will determine the impact of discount rate (0%-10%) on the cost utility ratio. We will also examine variability associated with the cost-utility ratio using a bootstrapping technique. The bootstrapping results will be presented using the acceptability curve approach. The acceptability curve shows the proportion of samples in which the intervention is considered cost-effective relative to a comparison condition given a maximum amount that a decision maker is willing to pay for the outcome (e.g., \$50,000/QALY). Specifically,  $\text{Net Benefit} = (-1) * (\text{Net Costs}) + (\text{Net Effects}) * (\text{Willingness to pay})$  is calculated and the proportion of samples with mean net benefit greater than zero is plotted across a range of willingness to pay values. If *mDAS* lowers costs and produces more health it will tend to have an acceptability curve over 50% across all levels of willingness to pay.

Sample Size Justification: Sample size calculations are powered to detect change in A1c. The ADA Technical Review of Diabetes Self-Management Education reported that successful education programs achieved reductions of 5-20% in A1c. The UKPDS 35 demonstrated that each 1% absolute reduction in mean A1c is associated with a 21% decrease in risk for any diabetes-related endpoint, a 21% decrease in diabetes-related deaths, a 14% decrease in risk for myocardial infarctions, and a 37% decrease in risk for microvascular complications. Based on our previous studies, we estimated a mean baseline A1c level of 10% with standard deviation of 1.8 and an effect size of  $(1.0/1.8) 0.56$  for Aim 1. The cross-time correlation was estimated to be 0.30 with compound symmetry structure. We adjusted for clustering and assumed an intraclass correlation coefficient (ICC) of 0.01 with five clusters. This yielded a design effect of 1.34. Two-sided alpha of 0.05 and 80% power were assumed. Allowing for 20% drop-out, 220 patients will be required total.

UI Health billing data show there are 7,258 adult African-Americans and Latinos with diabetes. We estimate that approximately half of these patients have an A1c level above 8.0% based on prior study. We anticipate recruiting 6% of the eligible diabetic population. We have successfully recruited a similar size of patients with type 2 diabetes using comparable recruitment methods.

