Cost and Healthcare Utilization Data: We will conduct a cost-utility analysis comparing *mDAS* with usual care, following the guidelines for conducting pharmacoeconomic analyses by the Panel on Cost-Effectiveness and Medicine and the International Society for Pharmacoeconomics and Outcomes Research. We will conduct the analysis from the health-system perspective, and include the costs of running the program as well as the costs associated with patient health services utilization. Costs will include pharmacists and HCs (training and implementation), educational materials, tablet computers with data service, text messaging, and videoconferencing. Health services utilization will include costs associated with hospital admissions, emergency room visits, outpatient visits and prescription medications during the intervention period. Participants will be followed throughout the study to obtain data on their programmatic and healthcare services related costs. At data collection points, research assistants will obtain the necessary information from patients on healthcare use outside of UI Health. We will capture UI Health care information electronically from the hospital electronic records and billing data for enrolled subjects. We have previously analyzed similar UI Health data. Additional costs (salaries for HCs, etc.) will be estimated from prevailing internal costs at the time. Cost estimations for healthcare use will be based on national Medicare reimbursement rates (average DRG rates) for hospitalization, Medicare fee schedules for physician and other professional services, and Medicare's Resource-Based Relative Value Scale for outpatient procedures. Since our study will span a period exceeding one year, appropriate costs will be discounted and adjusted for inflation.

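### The Aim 3 cost estimator treats study drop-out as the end of cost, and its present-value formula combines a monthly time index with an annual discount rate

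*Protocol*

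**What the plan says.** All of the following is in the Protocol.

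- **Time unit.** Under Cost and Cost Effectiveness in Section 12.0, "we will divide the time interval following randomization into months", and costs are cumulated to 6, 12, 18 and 24 months.
- **Weight.** The mean cost in month t among patients participating in month t is multiplied by the Kaplan-Meier probability of participating to that month. The event in this curve is leaving the study.
- **After drop-out.** "patients who drop out contribute costs from randomization through drop-out date (and then zero costs thereafter until end of subject follow-up". The same paragraph presents the method as accommodating drop-out and missing data, which it calls censoring.
- **Discounting.** Each month's weighted cost is divided by (1+r)^(t−1). No time unit is given for r at the formula. The next sentence reads "We will use a discount rate of 3% per year", and a later one reads "We will discount both QALYs and costs at 3% per year to maintain equivalent treatment of the measures of costs and effectiveness over time".
- **Sources of cost data.** Section 8.0 (Cost and Healthcare Utilization Data) includes both programme costs and health services use. It says "We will capture UI Health care information electronically from the hospital electronic records and billing data for enrolled subjects". Use outside UI Health is obtained from patients at data collection points.
- **QALYs.** QALYs and utilities are to come from a published Markov model. To compare them, "we will integrate the area under the Kaplan-Meier curves for each study condition to obtain mean QALYs".

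**The concern.** Weighting by the probability of being in the state where costs accrue is right when the event is death, because costs then stop. A living patient with uncontrolled diabetes who leaves the study goes on using care, and from the health-system perspective that the protocol adopts, this cost still counts. A zero is an observed value, not a censored one, so the rule contradicts its own stated purpose.

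The discounting problem is separate. A yearly rate raised to a power that counts months does not give 3% per year.

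Both faults lower the stated costs. Both can also distort the difference between arms, which is the numerator of the incremental ratio. Cost-effectiveness is a named aim, the ratio feeds the acceptability curve, and the results are meant to guide the sustainability plan.

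**Working it through.** **Inputs.** Monthly index, exponent t−1, r = 3% per year, weighting by participation, zero cost after drop-out and a 24-month horizon (all Section 12.0, Cost and Cost Effectiveness); 20% drop-out (Sample Size Justification); sensitivity range for the discount rate of 0% to 10% (same section). My assumptions: flat monthly cost, the 20% reached by month 24, several timings of drop-out, and every unequal split between arms.

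**1. Zero cost after drop-out.** Mean cost among participants times the probability of participating equals the mean over everyone with drop-outs counted as zero. The weight and the zero rule are therefore one and the same operation. With flat cost and no discounting, the share of true cost retained is the mean of S(t) over t = 1 to 24.

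- Linear loss, S(t) = 1 − 0.20 × t/24: share = 1 − 0.20 × 25/48 = 0.896, so 10.4% too low.
- Exponential loss, S(t) = 0.80^(t/24): 0.892.
- All loss in months 1 to 6: (6 − 0.7 + 18 × 0.8)/24 = 0.821, so 17.9% too low.
- All loss in months 13 to 24: (24 − 1.3)/24 = 0.946, so 5.4% too low.

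**2. Effect on the increment.** With equal true costs and linear loss, the false difference is the drop-out difference × 25/48.

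- 20% versus 20%: 0.
- 15% versus 25%: 0.10 × 25/48 = 5.2% of true 24-month cost.
- 10% versus 30%: 0.20 × 25/48 = 10.4%.

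The arm that loses more patients looks cheaper.

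**3. Discounting.** Entered literally, r = 0.03 with t in months gives 1.03^12 − 1 = 42.6% per year, which does not reproduce the stated 3%. The stated rate is recovered with the exponent (t−1)/12, or equivalently with a monthly r of 1.03^(1/12) − 1 = 0.247%. The table gives the share of a flat undiscounted cost retained, and in the second row the factor for month 24 alone.

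| Quantity | Literal, (t−1) | Stated rate, (t−1)/12 |
|---|---|---|
| 12 months, r = 3% | 85.4% | 98.7% |
| Month-24 factor, r = 3% | 0.507 | 0.945 |
| 24 months, r = 3% | 72.7% | 97.2% |
| 24 months, r = 10% | 41.2% | 91.4% |

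The literal error need not fall equally on the two arms, because mDAS is delivered in year 1 in one arm and in year 2 in the other. For the same flat programme cost in each delivery year, the year-1 factor is 0.854 and the year-2 factor is 0.854/1.426 = 0.599. The gap is 0.255 of a year's programme cost. At the stated rate it is 0.987 − 0.987/1.03 = 0.029.

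**4. Both together.** Linear 20% drop-out with literal discounting retains 66.0% of the undiscounted 24-month cost. With both corrected, 97.2% is retained.

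**The case against.** **On discounting.** The protocol states the annual rate twice, and r has no unit at the formula, so a careful analyst could enter the monthly equivalent and get the right answer. That stands. A reader might infer that the plan sets 3% per month; it does not. What remains is a printed formula that disagrees with the stated rate unless a conversion is made that the protocol never mentions.

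**On drop-out.** Section 8.0 speaks of enrolled subjects and does not say that records are followed after a patient leaves, and outside use depends on visits that drop-outs do not attend. Programme costs for mDAS may genuinely stop at drop-out. Both points stand, and both limit the remedy. Neither makes zero the right value for continuing healthcare use.

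**On unequal retention.** The protocol gives one overall figure of 20%, so the unequal splits above are illustrations only. One might point to the extra $50 payments, which in year 1 only the mDAS arm can earn. But under Transition and Retention the same payments go to the usual-care arm at 18 and 24 months, and every participant receives $30 per data collection. The schedule is symmetric over 24 months and does not establish that retention will differ.

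**On QALYs.** A reader might infer that the QALY side is wrong as well: that QALYs are discounted monthly, or that they are merely time in the study because participation is the only Kaplan-Meier curve defined. The text does not support this. No QALY discount formula is printed, the stated rate is annual, utilities have a named source in the Markov model, and nothing says that the curves to be integrated are the participation curves. If they are utility-weighted survival from the model, the error does not arise.

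**Conclusion.** The cost estimator is wrong as written in two respects.

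The drop-out rule is stated outright and needs no interpretation. At 20% drop-out it understates 24-month healthcare cost by about 10%, with a range of about 5% to 18% by timing, given flat monthly costs. It biases the increment when retention or costs differ between arms, and leaves it unbiased when both are equal.

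The discount formula is an internal inconsistency with a clear intent behind it. The fall to 72.7% describes what happens if the formula is programmed as printed, not a rate that the protocol sets.

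The QALY denominator is under-defined and not shown to be in error, so it would be too strong to say that both sides of the cost-utility ratio are wrong. The consequences are confined to Aim 3. The analyses of A1c, blood pressure, LDL-cholesterol and adherence, and the sample size, are untouched.

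**What to change.** 1. **Drop-out.** Replace the participation probability by the Kaplan-Meier probability of survival, with death as the event and drop-out as censoring. Take the mean monthly cost among patients alive and still observed, with no zeros entered after drop-out. Continue to extract UI Health records and billing data after drop-out where consent allows, and say how unreported outside use is handled. Cost mDAS delivery separately, since it may truly end when the patient leaves. Censoring still assumes that patients who leave cost much the same as those who stay; the billing data reduce that dependence.
2. **Discounting.** Write the divisor as (1+r)^((t−1)/12) with r = 0.03, or keep the exponent and state r as the monthly equivalent, about 0.247%. Apply the same convention across the 0% to 10% sensitivity range.
3. **QALYs.** Add one sentence saying that the curves to be integrated are utility-weighted survival from the Markov model and not the participation curves.

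The cost is a change of wording and formula, slightly more data extraction from sources already planned, and higher stated costs. No visit, sample-size or primary-analysis change is needed.

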## **4.0 Eligibility**

### **4.1 Inclusion Criteria**

- Self-identified as Latino/Hispanic or African-American
- Verbal fluency in English or Spanish
- Latest A1c  $\geq$  8.0% (within 3 mo)
- History of Type 2 Diabetes (> 1 year)
- Between the ages of 21 and 75 years
- Unlimited mobile phone/text messaging plan with ability to reply to text messages
- Home environment capable of video conferencing with wireless signal per patient's report of cell phone reception in the home
- Receives primary care at clinical site for at least one year, with one visit during past year
- Able and willing to provide informed consent (agree to data collection requirements, accept randomization, agree to home visitation with HC and pharmacist involvement, and participate for two years)

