## **6.0 Study Design and Procedures**

A randomized, controlled trial will evaluate the effectiveness of *mDAS* delivered by a clinical pharmacist and HC versus a usual care group. We will recruit 220 patients from UI Health. We recognize that all participants will have uncontrolled diabetes and require additional support from their healthcare team. Consequently, our usual care group will receive additional resources to meet basic standards of diabetes care and establish clinical equipoise between the two study groups. The usual care group will receive a referral to a diabetes educator and clinical pharmacist for medication reconciliation. These individuals are on staff and available to any patient, yet under-utilized. This group will receive a one-page contact sheet with the names and phone numbers of their local healthcare team as well as paper-based, low-literacy diabetes educational information. After one year, patients who have completed *mDAS* will be monitored for an additional year with usual care to evaluate maintenance, while the usual care patients receive *mDAS*. After recruitment, subjects will be randomized to receive either: (1) *mDAS* delivered by a clinical pharmacist and HC via home visits, videoconferencing, and text messaging; or (2) usual care. Study condition allocation will be completed after consent and baseline data collection. Using the REDCap Randomization Module, a random sequence of 220 subject assignments will be used. Blocked randomization (with varying block sizes) by clinical site, ethnic group (African-American and Latino), and gender will balance the proportion of participants.

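### Aim 3 compares costs by an unadjusted t-test that leaves out prior cost and the randomisation factors: an unbiased comparison, but less precise than the available data allow

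*Protocol*

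**What the plan says.** The cost plan is in Section 12.0, Cost and Cost Effectiveness. It will "estimate the cumulative costs from a health system perspective for each group over 24 months", and to do so it will "divide the time interval following randomization into months". Monthly mean costs are weighted by a Kaplan-Meier estimate of participation and discounted at 3% a year. The incremental average cost is then compared between arms by a two-sample t-test for independent groups. The only argument for the test concerns the shape of the distribution: "Costs may not be normally distributed; however, if the sample is sufficiently large", such "tests on untransformed costs are appropriate". Ratios are planned at 12 and 24 months.

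Three other places bear on the point:

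- Section 6.0 fixes the randomisation: "Blocked randomization (with varying block sizes) by clinical site, ethnic group (African-American and Latino), and gender will balance the proportion of participants".
- Section 8.0, Cost and Healthcare Utilization Data, names the source: "We will capture UI Health care information electronically from the hospital electronic records and billing data for enrolled subjects". It counts utilisation such as "outpatient visits and prescription medications during the intervention period" and defines no cost variable for the time before randomisation.
- Section 4.1 requires that a participant "Receives primary care at clinical site for at least one year, with one visit during past year".

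**The concern.** A patient's earlier health-care cost usually predicts later cost, and costs are skewed, with a few heavy users. When a predictive baseline variable is left out, its chance variation between arms stays in the standard error of the cost difference. Leaving out the randomisation factors has a similar effect: the stratified blocks remove between-arm variation that the t-test's standard error still counts.

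What is at stake is the width of the interval around the cost increment, and so around the within-trial cost-effectiveness ratios and the net benefit. The sample size in Section 12.0 is set for A1c; no precision is stated for cost. A wide cost interval is therefore likely, and precision available at little expense is worth having.

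**Working it through.** **Is the adjustment made elsewhere?** No.

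- The opening of Section 12.0 puts random effects for site, PCP and health coach, and covariates, into the effectiveness models. A two-sample t-test has no place for them.
- The secondary analyses for unequal baseline variables, under Primary Outcomes, belong to the MANOVA of physiological outcomes.
- The economic sensitivity analyses vary factors such as age, visit rates and discount rate. The bootstrap describes sampling variability. Neither adjusts cost for baseline.

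**Inputs from the protocol.** 220 patients with 20% drop-out leave 220 × 0.80 = 176, or 88 per arm if allocation is 1:1 (assumed). Four to six sites × 2 ethnic groups × 2 genders (taken as two) make 16 to 24 strata. There is no figure of the plan's own to reproduce, because no cost SD, prior-to-trial cost correlation or cost power is given. The correlation r and the coefficient of variation (CV) below are assumptions.

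**Effect of adjusting for prior cost.** Variance ratio, adjusted to raw, = 1 − r². Interval-width ratio = √(1 − r²). Equivalent N = 176 / (1 − r²).

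| r (assumed) | Variance ratio | Width ratio | Equivalent N |
|---|---|---|---|
| 0.2 | 0.96 | 0.98 | 183 |
| 0.3 | 0.91 | 0.95 | 193 |
| 0.4 | 0.84 | 0.92 | 210 |
| 0.5 | 0.75 | 0.87 | 235 |

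**Under skew.** Simulated log-normal costs, 110 per arm, with log prior cost as covariate:

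- Log SD 1.0: variance ratio 0.907 at r = 0.30 and 0.776 at r = 0.49. The interval is narrower by 1 − √0.907 = 5% and 1 − √0.776 = 12%.
- Log SD 1.3 (heavier tail), correlations of about 0.3 to 0.5: variance ratios 0.951 and 0.843, cuts of 5% and 16%. The interval is narrower by 1 − √0.951 = 2.5% and 1 − √0.843 = 8%.

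A second simulation (88 per arm, log SD 1.2, raw prior cost as covariate) gave standard-error ratios of 0.98, 0.91 and 0.79 at realised r of about 0.20, 0.36 and 0.57.

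A closed-form check of the heavier-tailed case uses log SD s and log-scale correlation ρ. Then r = (exp(ρs²) − 1)/(exp(s²) − 1), and the fraction of variance removed by log prior cost is ρ²s²/(exp(s²) − 1). With s = 1.3, s² = 1.69 and exp(1.69) − 1 = 4.42. At r = 0.3, ρ = 0.50 and the cut is 0.25 × 1.69/4.42 = 10%. At r = 0.5, ρ = 0.69 and the cut is 0.476 × 1.69/4.42 = 18%. The simulated 5 to 16% is thus on the cautious side, and both sets lie within 4 to 25%.

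**In terms of mean cost.** The raw 95% half-width is 1.96 × CV × √(2/88). With CV = 2 (assumed) it is 1.96 × 2 × 0.151 = 59% of mean cost. At r = 0.5 it becomes 59% × 0.866 = 51%.

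**Effect of ignoring the strata.** If they explain a fraction R² of cost variance (assumed), the actual two-sided level of a nominal 5% test is 2[1 − Φ(1.96/√(1 − R²))]. This is 0.049, 0.044 and 0.039 at R² = 1%, 5% and 10%. The standard error would fall by 0.5 to 5% on adjustment.

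**The case against.** The strongest reply is that nothing stated is wrong. Under randomisation the raw mean difference is unbiased, the test does not produce excess false positives from this cause, and covariates for a non-primary comparison are often left to an analysis plan, which is not shown here. All of this stands except the last part: the protocol names the test, so the choice has been made rather than deferred.

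Further points stand and limit the claim:

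- **Chance imbalance is not a second harm.** A one-standard-error imbalance in prior cost moves the raw difference by r × 0.151 SD, or 0.045 to 0.075 SD at r = 0.3 to 0.5. That is 0.3 to 0.5 of the raw standard error, so the raw interval already covers it. It is the same loss of precision restated. Stratified blocks also limit imbalance on site, ethnic group and gender.
- **Prior billing is an imperfect covariate.** Trial cost includes programme cost and use outside UI Health; prior UI Health billing holds neither. Eligibility guarantees only one visit in the past year.
- **A careless regression could do damage.** A plain regression of each patient's 12-month total would drop the Kaplan-Meier allowance for drop-out and the 24-month ratio.

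A reader might infer that the cost increment is biased, or that the sentence defending untransformed costs is mistaken. The documents support neither. That sentence concerns non-normality, and the arithmetic mean difference is the right quantity to keep. Nor does the point reach every ratio equally: cost per QALY also rests on projections beyond the trial.

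**Conclusion.** The point holds as an optional gain in precision, not as a correction of bias. The named t-test leaves out the randomisation factors and prior cost, and no other part of the protocol brings them into the cost comparison. The result remains unbiased and at worst slightly conservative.

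The size rests wholly on assumed correlations. At 0.2 to 0.5 the variance falls by about 4 to 25% and the interval narrows by 2 to 13%. With heavy-tailed costs, the simulated gain is about 5 to 16% in variance and 2.5 to 8% in width. At a correlation of 0.2 or below the gain is negligible. The gain from the strata alone is small unless they explain 5 to 10% of cost variance, which is also assumed.

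**What to change.** In Section 12.0, Cost and Cost Effectiveness, replace the t-test with a linear regression of untransformed discounted cost on arm, as follows:

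1. Adjust for clinical site, ethnic group, gender and UI Health cost in the 12 months before randomisation. Enter prior cost as a log or in bands, so that a few extreme values do not dominate, and define the variable and its extraction in Section 8.0.
2. Keep the allowance for drop-out, for example by inverse-probability-of-censoring weights from the Kaplan-Meier participation estimate.
3. Apply the regression at both 12 and 24 months.
4. Take intervals from the bootstrap already planned, refitting the adjusted model in each resample.
5. Use the adjusted increment in the within-trial cost-effectiveness ratios and the net benefit. Keep the unadjusted comparison as a sensitivity analysis.

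The cost is one more year of extraction from the same billing source, after confirming that the patients' authorisation covers it, and slightly more analysis work. No patients or visits are added. If the extraction is not authorised, adjust for the randomisation factors and for the comorbidity, complication, therapy and insurance variables already collected at baseline under Section 8.0. The choice should be written down before cost data are examined by arm, so that covariates are not picked in the light of results.
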